**3.3. Randomization**

The sample of children with CP will be divided into two groups: PC1 and PC2, with individual random assignment of participants to each group in blocks of 4 or 8 children. This assignment will be carried out using a specific program coded in Matlab software. A control sample of TD children (n=32) will be matched for age and sex with the children with CP.

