**3.2.1. Inclusion Criteria**

**For children with CP:**

- Age between 18 months and 5 years and 6 months
- CP of spastic diplegia or spastic hemiplegia type, GMFCS I to II
- No or moderate contracture of the triceps surae (ankle dorsiflexion: > 5° during clinical examination, knee extended)
- Sufficient level of understanding to perform the activities involving the trunk in the form of self-exercises (rehabilitation protocol) as well as the clinical assessments and functional explorations.
- Acceptance of the physical therapist in charge of the child's follow-up to collaborate in the implementation of the RAIT
- Affiliated with a social security scheme

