**3.2.3. Sample Size Calculation**

The calculation of the number of subjects needed is based on the primary endpoint. The distribution of the peak sternum deceleration at the beginning of the stance phase was Gaussian in our previous study. On average, this distribution was centered on 3.0 ± 1.1 m.s-2 (mean ± 1 standard deviation) in children with CP and on 1.1 ± 0.3 m.s-2 in TD children (24). The expected effect of RAIT is a minimum reduction in the peak sternum deceleration at the beginning of the stance phase of one-third of its value, similar to the effect of RAIT in the previous study (24). To demonstrate an effect of RAIT using a repeated measures ANOVA in which we expect a small effect size, with an alpha level set at 0.05 and a power of 80%, a total sample size of 24 patients, i.e., 12 per group, is necessary (calculation performed using G*Power 3.1 software; **Figure 3).** We expect greater variability in dynamic gait variables (expected in children aged 18 months to 5 years and 6 months compared to children aged 5 to 12 years). Therefore, we plan to recruit 32 children with CP (16 per group), to account for this greater variability and to compensate for potential dropouts.

[figure not shown]

**Figure 3:** Calculation of the number of subjects needed, performed using G*Power 3.1 software.

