**4.5. Statistical Analysis Plan**

Statistical analyses will be performed using general linear models, as the overall sample size (N=64) and the size of each group (n=32) are considered sufficient for applying such procedures. The conditions for using these tests will be verified beforehand, particularly the normal distribution of residuals (using quantile-quantile plots and Shapiro-Wilk tests) and the homogeneity of variance (Levene's tests). If the data do not meet these conditions, non-parametric equivalents will be used.

In the first phase, the group effect (Children with CP vs. TD Children) will be analyzed using multivariate analysis of variance (MANOVA) procedures on the dependent kinematic (step width), dynamic (sternum and L5 decelerations and anterior foot position during the 1st double-support phase), and clinical (ECAB, GMFM-66-IS, and "Reaching Hand" questionnaire) variables. A multiple linear regression analysis will also be performed, with the anterior foot position during the 1st double-support phase as the dependent variable and the sternum and L5 decelerations at the beginning of the stance phase as the regressors.

Furthermore, the effects of the specific rehabilitation (2 Groups x 4 Periods) will be tested using the same type of multivariate procedures (MANOVA) and a 2 Groups [PC1 vs. PC2] × 4 Periods [M0, M3, M6, M12] mixed design, with a particular focus on the Group × Period interaction. If this interaction is significant, the analysis of local comparisons using post-hoc procedures (Tukey's tests) will allow us to examine: 1) the significance of the rehabilitation (significant difference between the two groups at M3 with a reduction in the peak sternum deceleration at the beginning of the stance phase for the group that underwent RAIT between M0 and M3); 2) the reproducibility of the RAIT effect (similar differences between M3 and M6 for the RH-RAIT group and between M0 and M3 for the RAIT-RAIT group); and 3) the enhancement of the RAIT effect when it is continued (between M6 and M0 versus between M3 and M0, and between M12 and M0 versus between M6 and M0 for the RAIT-RAIT group; and between M12 and M3 versus between M6 and M3 for the RH-RAIT group).

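### The randomised PC1–PC2 comparison uses age neither in allocation nor in the model, which leaves chance age imbalance and avoidable imprecision (not bias) in the M3 contrast

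*Protocol*

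**What the plan says.** - **Population (3.2.1).** Children with CP are eligible over a four-year span: "Age between 18 months and 5 years and 6 months". Two clinical types enter: "CP of spastic diplegia or spastic hemiplegia type, GMFCS I to II".
- **Sample size (3.2.3).** The calculation gives 24 children. The protocol then states "We expect greater variability in dynamic gait variables", comparing this age band with the 5–12-year-olds of the previous study, and concludes: "Therefore, we plan to recruit 32 children with CP (16 per group), to account for this greater variability and to compensate for potential dropouts".
- **Allocation (3.3).** Children with CP are allocated "with individual random assignment of participants to each group in blocks of 4 or 8 children". No stratification or minimisation factor is named. Age and sex are used only for the non-randomised controls: "A control sample of TD children (n=32) will be matched for age and sex with the children with CP".
- **Model (4.5).** PC1 and PC2 are compared in "a 2 Groups [PC1 vs. PC2] × 4 Periods [M0, M3, M6, M12] mixed design", first through the Group × Period interaction. If that is significant, Tukey comparisons follow, and the rehabilitation effect is read from the difference between the two groups at M3. No covariate is named.

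**The concern.** The protocol gives the young age band as a reason to expect more variability and responds with more children. Age is known exactly for every child before allocation, so it could be used at almost no cost, but the randomised comparison does not use it. With 16 per arm and a four-year span, one arm can easily turn out noticeably older. If the endpoint varies with age within this band, such a gap moves the observed M3 difference, and the age-related spread stays in the error of that contrast. If change over three months also depends on age, part of an imbalance carries into the M0–M3 change, and the M0 value alone does not remove it.

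At stake are the precision of the primary result and how easily a chance age difference can be separated from the effect of RAIT.

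**Working it through.** **1. The protocol's own figure.** The text gives neither Cohen's f nor the correlation between repeated measures. For a within–between interaction with 2 groups and m = 4 periods, λ = f²·N·m/(1 − ρ), with 3 and 3(N − 2) degrees of freedom. Assuming f = 0.25 and ρ = 0.5, N = 24 gives λ = 0.0625 × 24 × 4 / 0.5 = 12 and power 0.816. The stated 24 is therefore reproducible under those assumptions. The calculation contains no age term.

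**2. Chance imbalance in age at 16 per arm.** The protocol gives no age distribution.
- Uniform over 18–66 months: SD = 48/√12 = 13.9 months. SE of the difference in means = 13.9 × √(2/16) = 4.9 months. P(gap > 6 months) = P(|Z| > 1.22) = 22%; P(gap > 8 months) = 10%.
- Uniform over 30–66 months, if few very young children qualify: SD = 36/√12 = 10.4, SE = 3.7 months. P(gap > 6) = 10%; P(gap > 8) = 3%.

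**3. Where age enters the analysis.** In a simulation of the 2 × 4 design (16 per arm, variance 1 before any age effect, correlation 0.5):

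| Age effect | Within-child mean square (Group × Period) | Between-child mean square |
| --- | --- | --- |
| none | 0.50 | 2.50 |
| constant, 0.5 per year | 0.50 | 3.82 |
| age-dependent change over periods (illustrative) | 0.52 | 2.63 |

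A constant age effect thus leaves the interaction test untouched and acts on between-child comparisons, which include PC1 against PC2 at M3. Only age-dependent change reaches both.

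**4. Size for the M3 contrast.** Inputs from 3.2.3: SD 1.1 m/s² and an effect of one-third of 3.0, that is 1.0 m/s². There are 16 per arm; the test is a plain two-sided t-test at 5%. It includes neither the Tukey adjustment nor the gating by the interaction, so the figures serve for comparison only. Unadjusted: noncentrality = 1.0/(1.1 × √(2/16)) = 2.57 on 30 df, power 70%. With age in the model, residual SD = 1.1 × √(1 − r²) on 29 df, where r is the assumed age–endpoint correlation. The shift from a six-month gap in mean age is r × 1.1/13.9 × 6.

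| r (assumed) | Residual SD | Power with age | Shift in the M3 difference from a 6-month gap |
| --- | --- | --- | --- |
| 0.2 | 1.08 | 72% | 0.10 m/s² |
| 0.3 | 1.05 | 74% | 0.14 m/s² |
| 0.5 | 0.95 | 82% | 0.24 m/s² |
| 0.6 | 0.88 | 87% | 0.29 m/s² |

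At r = 0, the lost degree of freedom costs about 0.1 point. Allowing also for chance correlation between age and arm (variance × (1 + 1/28)), power falls to about 69%, a loss of under 2 points.

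**5. Form of the covariate.** In a random-intercept model fitted to simulated 2 × 4 data, age as a main effect alone left the estimated group difference in M0–M3 change unchanged (−1.852 with and without it). Adjusting that change requires an age × Period term.

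**6. Alternative model.** Analysing M3 with M0 as covariate, at an assumed M0–M3 correlation of 0.5, gives 82% power. Adding age raises this to 83% at a partial R² of 0.03 and to 93% at 0.30. These R² values are also assumptions.

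**The case against.** The strongest reply is that unstratified blocking of 32 children at one centre is legitimate, that the 5% error rate already covers chance imbalance, and that a covariate list may be left to a separate analysis plan. The first two parts stand: validity is not in question. The third stands only in part. Section 4.5 is itself headed as the statistical analysis plan and writes out the model, and stratification has to be set before the first inclusion.

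Four stronger readings are tempting, and the documents do not support them.
- **Age variance inflates the error of the Group × Period test.** Mostly not: a constant age effect cancels within child, and that interaction is the gating test. Only age-dependent change remains in it.
- **The increase from 24 to 32 could be replaced by a covariate that explains a quarter of the variance.** The increase is also meant to cover dropouts, and no covariate replaces lost children.
- **The protocol shows that age within 18 months to 5.5 years drives the endpoint.** It compares this band with 5–12-year-olds. It gives no age correlation within the band and no rate of change over three months. Extra variability within or between young children of the same age would not be removed by an age term.
- **CP type is a prognostic factor that has been ignored.** The rule in 3.2 on which limb to analyse in diplegia is a measurement convention; the protocol documents no prognostic effect.

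It is also fair that the requirements for independent walking and sufficient understanding may thin out the youngest children, which lowers the imbalance figures as shown.

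**Conclusion.** The point holds as one of precision and chance imbalance. The allocation and the written model leave unused a baseline value that the protocol itself links to variability, and the M3 contrast, from which the effect is judged, is exposed to it. A reader might infer that the comparison is biased; it is not, because randomisation keeps the test valid.

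Under the assumed uniform age range, a gap in mean age above 6 months occurs in 22% of allocations, or 10% if the youngest children are few. Adjustment gains 2 to 4 power points at correlations of 0.2 to 0.3, and 12 to 17 points at 0.5 to 0.6, from a base of 70%. Since the protocol gives no correlation, a small gain is quite possible. The change is still worth making because it costs almost nothing.

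**What to change.** **In 4.5:** include age at M0 (continuous) in the PC1–PC2 model together with an age × Period term. Alternatively, for the RAIT–RH comparison, analyse the M3 value with M0 and age as covariates. An age main effect alone is not enough. CP type (hemiplegia or diplegia) may be added in the same way, as an option rather than a requirement.

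**In 3.3:** if inclusion has not begun, have the Matlab program draw separate block lists for two age strata, and keep the stratum or continuous age in the model. If inclusion has begun, change the model only.

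**Cost:** a sentence or two in 4.5, a redrawn list and no extra measurements. The model loses one or two between-child degrees of freedom, about 0 to 2 power points if age turns out to be irrelevant. If both strata stop mid-block, arm sizes could differ by up to 4 with blocks of 4 (2 per stratum) or up to 8 with blocks of 8 (4 per stratum), which favours the smaller blocks.

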**2.3. Secondary Objective(s) and Hypotheses**

The secondary objectives, for the secondary endpoints described in paragraph 2.4 below, aim to: (1) show an impairment of these criteria in the study's children with CP compared to typically developing (TD) children; (2) show a significantly greater improvement in these criteria after 3 months of RAIT than after 3 months of RH; (3) show a further improvement in these criteria when the duration of RAIT is increased.

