**For TD children:**

- Age between 18 months and 5 years and 6 months
- Walking acquired before the age of 18 months
- Sufficient level of understanding to perform the clinical assessments and functional explorations
- Affiliated with a social security scheme

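### TD controls are matched to the CP children on age and sex, but the CP-TD MANOVA carries neither factor, so this secondary comparison may lose precision across a four-year age span

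*Protocol*

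**What the plan says.** Protocol section 3.3 (Randomization) sets up the control group: "A control sample of TD children (n=32) will be matched for age and sex with the children with CP". It does not say whether matching is child by child or by group frequencies, and it gives no age tolerance.

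The TD age criterion in section 3.2.1 is "Age between 18 months and 5 years and 6 months", and the CP children have the same range.

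Section 4.5 fixes the model: "the group effect (Children with CP vs. TD Children) will be analyzed using multivariate analysis of variance (MANOVA) procedures". Its dependent variables are step width, sternum and L5 decelerations, anterior foot position in the first double support, ECAB, GMFM-66-IS and the Reaching Hand questionnaire. No age, sex or pair term is named. The same section treats the data as two groups: "the overall sample size (N=64) and the size of each group (n=32) are considered sufficient".

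The comparison serves the first secondary objective in section 2.3: "show an impairment of these criteria in the study's children with CP compared to typically developing (TD) children".

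**The concern.** Matching on age and sex balances those factors between the groups. It does not remove their contribution to the spread within each group. A two-group MANOVA without those factors counts that spread as error.

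The protocol itself gives reason to expect age effects. Its Scientific Context says trunk control develops progressively through childhood, and section 3.2.3 expects more variable gait dynamics at these ages than at 5 to 12 years.

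At stake is precision. A real CP impairment on a variable with a moderate gap and a clear age trend could be missed, although the design had already done the work of matching.

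**Working it through.** **The plan's own figure.** There is none to reproduce. Section 3.2.3 sizes the trial for the rehabilitation effect only; no power or precision is given for CP versus TD.

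**Inputs from the protocol.** 32 children per group (3.3, 4.5). Age span 5.5 − 1.5 = 4.0 years (3.2.1). Peak sternum deceleration "centered on 3.0 ± 1.1 m.s-2 (mean ± 1 standard deviation) in children with CP and on 1.1 ± 0.3 m.s-2 in TD children" (3.2.3, from the previous study in children aged 5 to 12), so a gap of 3.0 − 1.1 = 1.9 m.s-2.

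**Assumed input.** The correlation r between matched CP and TD values that is due to age and sex. It is not in the protocol and is varied below.

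**Formulas.** With group SDs s1 and s2:
- SE ignoring matching = √[(s1² + s2²)/32]
- SE using matching = √[(s1² + s2² − 2·r·s1·s2)/32]

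With equal SDs the ratio is 1/√(1 − r). The same form covers frequency matching with a common age slope: the ratio is 1/√(1 − R²), where R² is the share of within-group variance explained by age and sex.

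**Equal SDs.**
- r = 0.2: 1/√0.8 = 1.118, SE about 12% too large
- r = 0.3: 1/√0.7 = 1.195, about 20%
- r = 0.5: 1/√0.5 = 1.414, about 41%

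**Sternum SDs 1.1 and 0.3.** s1² + s2² = 1.21 + 0.09 = 1.30, and 2·s1·s2 = 0.66. SE ignoring matching = √(1.30/32) = 0.202.
- r = 0.2: √(1.168/32) = 0.191, ratio 1.055, about 5%
- r = 0.3: √(1.102/32) = 0.186, ratio 1.086, about 9%
- r = 0.5: √(0.970/32) = 0.174, ratio 1.158, about 16%

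For the sternum, t = 1.9/0.202 ≈ 9.4 even with matching ignored, so power is close to 100% either way.

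**Direction and power, by simulation** (32 pairs, equal SDs, nominal two-sided 0.05, 40,000 runs; d = 0.6 is an illustrative standardized gap):

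| r | Type I error, unpaired | Type I error, paired | Power at d = 0.6, unpaired | Power at d = 0.6, paired |
|---|---|---|---|---|
| 0 | 0.051 | 0.052 | 66% | 64% |
| 0.1 | 0.039 | 0.051 | 66% | 69% |
| 0.3 | 0.021 | 0.050 | 68% | 79% |
| 0.5 | 0.0065 | 0.048 | 72% | 91% |

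For a joint test on seven outcomes (5,000 runs, correlation of 0.4 assumed between outcomes), the unpaired type I error is 0.049, 0.008 and 0.002 at r = 0, 0.3 and 0.5. The paired test stays between 0.052 and 0.055.

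**Endpoints reached.** Section 2.4 lists nine secondary endpoints. Five are in the CP-TD MANOVA: step width, L5 deceleration, anterior foot load (taking the anterior foot position of 4.5 to be this variable), ECAB and GMFM-66-IS. The protocol states no CP-TD gap for any of them. The other four are eGVI, the two standing-sway variables and the Edinburgh score; they are not in that MANOVA.

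**Error degrees of freedom.** Two groups: 64 − 2 = 62. With age and sex as covariates: 62 − 2 = 60. With 32 pairs as blocks: 32 − 1 = 31.

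**The case against.** The strongest reply is that an unadjusted comparison of matched groups is valid, merely less efficient, and that covariates for a secondary comparison belong in a separate analysis plan. The first half stands: there is no bias if the balance holds, and no excess of false positives when the shared factor acts in the same direction in both groups. The second half stands only in part. Section 4.5 does not leave the model open; it names the procedure, the dependent variables, the assumption checks and the post-hoc tests. The general linear models it announces could take covariates, but none is named.

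It also stands that the size is assumed. The protocol gives no correlation, and no SD or age slope for the five variables at issue. Step width is already normalized to pelvis width, which may remove some of its growth-related spread. At r = 0 nothing is lost.

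Three stronger readings are tempting, and the protocol supports none of them:
- A reader might infer that each control is individually paired with a CP child. In section 3.3 the word individual describes the randomization ("with individual random assignment of participants to each group in blocks of 4 or 8 children"). Equal group sizes fit pairing and frequency matching alike.
- A reader might infer that the error estimates are wrong in a way that produces false claims. With positive correlation they err only towards caution.
- A reader might infer that all nine secondary endpoints are affected. This MANOVA contains five of them.

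**Conclusion.** The point holds as a modest loss of efficiency in a stated secondary analysis. The design controls age and sex, the model omits them, and both groups span four years of early development. The excess in the standard error is about 12% to 41% with equal SDs and r from 0.2 to 0.5, or about 5% to 16% with the sternum SDs, which come from older children. For sternum deceleration the effect is immaterial. It could matter for the five MANOVA variables with no stated gap, if they follow age and their CP-TD differences are moderate. The conclusion assumes that matching achieves balance and that age acts in the same direction in both groups. The randomized comparison of RAIT with RH does not depend on any of this. This is a low-priority but nearly free improvement.

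**What to change.** In section 4.5, estimate the CP-TD group effect with age and sex as covariates, either as a MANCOVA or as one linear model per endpoint. This works under individual or frequency matching, uses data the matching already requires, and costs about two error degrees of freedom (62 to 60).

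In section 3.3, state which type of matching is meant. Use the pair as a block only if matching is truly 1:1, and acknowledge that this leaves about 31 error degrees of freedom instead of 62, a real cost with seven outcomes.

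The change is to the wording only; no visit, measurement or sample size is affected.

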**3.4. Experimental Plan**

The project includes a clinical examination and instrumental functional explorations at four time points. The experimental plan is shown in Figure 4. The assessments are described in chapter "4.3. Measurements – Description of assessments performed during the research." Assessments will be conducted at M0, M3 (M0 + 3 months), M6 (M0 + 6 months), and M12 (M0 + 12 months) for children with CP and at M0 for TD children. Thus, three rehabilitation periods will be planned: the first between M0 and M3, the second between M3 and M6, and the third between M6 and M12. A first group of children (group PC1) will continue their usual rehabilitation (RH) for the first 3 months and then will have RAIT for the following 9 months (PC1 = RH-RAIT). The second group of children, PC2, will immediately have RAIT for the 12 months of the study (PC2 = RAIT-RAIT). As the previous study conducted in children with CP aged 5 to 12 years showed a therapeutic effect only related to RAIT (and not to RH), RAIT will be continued for the children who benefited from it from the first 3-month period and for all children for the last 9 months of the study. Such a plan will allow to: 1) ensure that all children with CP benefit from RAIT; 2) measure the effect of RAIT over 3 months compared to that of RH; 3) test the reproducibility of the effect of RAIT over 3 months between the two groups and 4) test the effect of an additional 3 months of RAIT in the PC2 group (M6 versus M3) and 6 months in both groups (M12 versus M6) (**Figure 4**).

[figure not shown]

**Figure 4:** Experimental plan of the study. RAIT: rehabilitation through postural activities involving the trunk; conventional rehabilitation is based on the treatment of muscle groups (stretching, strengthening, tone reduction) of the lower limbs

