**ActivTronc Protocol**

**1. Scientific Context**

Cerebral palsy (CP) describes a group of permanent motor and postural disorders that limit activity, caused by lesions to the developing brain in utero or post-partum. Subsequent reorganizations of central nervous system functions in children with CP also lead to motor disorders (1). The typical development of segmental trunk control, which occurs progressively during childhood (2), is closely linked to gross motor performance in young infants (3) and is significantly delayed in premature infants (4). From early infancy, children with CP exhibit axial control disorders and abnormal postural control in a sitting position (5). We recently showed that children with CP had specific impairments in trunk control during a self-stabilization task on an unstable sitting device compared to typically developing (TD) children (6). These deficits in axial postural control (and particularly in trunk control) remain present throughout the motor development period—even after the child can stand and walk independently (7).

During walking, children with CP show significant deviations in trunk kinematics and kinetics; the ranges of motion of the trunk in all three planes of space are much larger than in TD children (8). These deviations are associated with poor dynamic balance control during walking (9), resulting in wider step widths (10), greater variability in step length, greater accelerations of the head, thorax (upper trunk), lower back (L3 region), pelvis, and the body's center of mass in all three planes throughout the gait cycle, and greater lower back instability compared to TD children (11,12). Since the trunk and lower limbs interact reciprocally during walking, in children with CP, trunk deviations lead to lower limb deviations, and vice versa (7,13).

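### Secondary objective 3 (longer RAIT) rests on within-group changes while every child is on RAIT, so maturation can pass for benefit; the randomised M6 and M12 contrasts are not named for it

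*Protocol*

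**What the plan says.** Secondary objective 3 (Protocol, section 2.3) is to "show a further improvement in these criteria when the duration of RAIT is increased", for the endpoints of section 2.4.

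Section 3.4 turns this into two comparisons: to "test the effect of an additional 3 months of RAIT in the PC2 group (M6 versus M3"), and the effect of "6 months in both groups (M12 versus M6"). Section 4.5 restates them as differences between changes, for example "between M12 and M0 versus between M6 and M0 for the RAIT-RAIT group".

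Section 3.4 puts PC1 on usual rehabilitation (RH) until M3 and then on RAIT; PC2 has RAIT throughout. RAIT is given "for all children for the last 9 months of the study". TD children are assessed at M0 only. The inclusion criterion is "Age between 18 months and 5 years and 6 months", and section 1 refers to "The typical development of segmental trunk control, which occurs progressively during childhood".

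In section 4.5, Tukey post-hoc comparisons follow only if the Group × Period interaction in the 2 × 4 design is significant. The one between-group comparison named there is at M3. Reproducibility is to be seen in "similar differences between M3 and M6 for the RH-RAIT group and between M0 and M3 for the RAIT-RAIT group".

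**The concern.** A change from M3 to M6, or from M6 to M12, in children who are all on RAIT is the sum of three things: any effect of further RAIT, normal development, and growing familiarity with the tests. The design has no group without RAIT in those windows, and no TD follow-up, to separate them. In children this young, with balance and gross motor scores among the endpoints, the second and third parts may not be small. At stake is one of the three secondary objectives: a claim that longer RAIT brings further gain could rest on development alone.

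The delayed-start design also holds randomised comparisons of duration, at M6 and M12, in which development common to both groups cancels. Section 4.5 ties neither to an objective.

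The reproducibility check sets one group's change beside the other's in a different time window, with no stated way to contrast them and no criterion for *similar*.

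**Working it through.** **1. What the duration contrasts reduce to**

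- (M6 − M0) − (M3 − M0) = M6 − M3, in PC2.
- (M12 − M0) − (M6 − M0) = M12 − M6, in PC2.
- (M12 − M3) − (M6 − M3) = M12 − M6, in PC1.

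Subtracting the earlier visit removes it; it does not supply a control. Each is a before-after change in one group.

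**2. RAIT received by each visit**

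| Visit | PC1 | PC2 | Randomised contrast |
|---|---|---|---|
| M3 | 0 months | 3 months | named in 4.5 |
| M6 | 3 months | 6 months | not named |
| M12 | 9 months | 12 months | not named |

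**3. Inputs**

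From section 3.2.3: mean 3.0 and SD 1.1 m/s² for sternum deceleration in children with CP aged 5 to 12; expected reduction one-third, so 3.0/3 = 1.0 m/s²; 16 per group planned. The protocol gives no calculation for objective 3, so there is no figure of its own to reproduce.

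Assumed, because the document gives neither: correlation between visits ρ from 0.3 to 0.8, and favourable drift of 0.1 to 0.3 m/s² per 3 months. The endpoints in section 2.4 have no SD in the protocol, so the figures below illustrate the problem on the primary endpoint.

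**4. Bias and false findings**

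With no extra benefit of longer RAIT, the bias equals the drift: 0.1 to 0.3 for M6 − M3, and 0.2 to 0.6 for M12 − M6. The 2 × 4 design was simulated (8,000 runs per scenario, 16 per group) with a true RAIT effect of 1.0 in its first 3 months and none after. Entries are percentages of trials for drift 0.1 / 0.2 / 0.3:

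| Result | ρ = 0.5 | ρ = 0.8 |
|---|---|---|
| Interaction gate opens | 73 / 73 / 73 | 99 / 99 / 99 |
| Gate opens and pooled M12 vs M6 favours longer RAIT | 12.4 / 38.0 / 62.5 | 33.9 / 87.5 / 99.0 |
| Gate opens and Tukey M12 vs M6 in PC2 | 1.1 / 4.5 / 15.0 | 2.9 / 21.2 / 63.2 |
| Gate opens and Tukey M6 vs M3 in PC2 | 0.0 / 0.3 / 1.0 | 0.6 / 2.9 / 8.8 |
| Randomised PC2 vs PC1 at M6 (true difference 0) | 4.8 / 5.4 / 4.9 | 4.8 / 5.1 / 4.9 |

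If RAIT has no effect at all, the gate opens in about 5% of trials and the gated pooled finding occurs in 0.9% to 4.9%.

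**5. Precision of the reproducibility contrast, (PC1: M6 − M3) − (PC2: M3 − M0)**

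SD of a change = 1.1 × √(2(1 − ρ)); SE = SD × √(2/16); half-width = t(0.975, 30) × SE, with t = 2.042.

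- ρ = 0.3: SD 1.30, SE 0.460, half-width 0.94.
- ρ = 0.5: SD 1.10, SE 0.389, half-width 0.79.
- ρ = 0.7: SD 0.85, SE 0.301, half-width 0.62.

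At ρ = 0.5, two identical observed changes of 1.0 would leave a PC1 change smaller by 0.79, about 0.2, inside the interval.

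**6. Precision of the randomised M6 contrast**

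- Baseline-adjusted half-width at ρ = 0.5: t(0.975, 29) × 1.1 × √(1 − 0.25) × √(2/16) = 2.045 × 0.337 = 0.69. The within-PC2 change has 2.131 × 1.1/√16 = 0.59.
- Difference detectable with 80% power: 2.80 × 1.1 × √(1 − ρ²) × √(2/16) = 0.94 at ρ = 0.5 and 0.65 at ρ = 0.8. With 12 completers per group these become 1.09 and 0.75.
- Power for an extra effect of 0.5 m/s², 16 per group: 0.32 at ρ = 0.5 and 0.57 at ρ = 0.8.

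**The case against.** A reader might infer that objective 3 is almost bound to be declared met whether or not longer RAIT helps. The document does not support that. Drift common to both groups produces no interaction, so the gate protects when RAIT does nothing. Tukey's correction keeps false M6-versus-M3 findings at or below about 9% in the scenarios above. High rates appear mainly for M12 versus M6, with larger assumed drift and higher correlation. The protocol gives no developmental slope for any endpoint, so maturation *can* read as benefit; it is not shown that it will. What remains is that neither gate nor Tukey removes the bias from the estimate, and the gate opens precisely when RAIT works early.

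A reader might also infer that the randomised M6 and M12 data go wholly unused. They enter the omnibus interaction, and an all-pairs Tukey procedure would include them. The accurate criticism is that they are not named or linked to objective 3.

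Nor does section 4.5 say that a non-significant test proves similarity. The gap is narrower: Tukey tests of cell means do not directly contrast two changes, and no criterion is set.

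*Uncontrolled* would be too broad for the reproducibility check as a whole. PC2's change from M0 to M3 has a concurrent randomised RH control, and PC1's RH period records a 3-month change without RAIT. That period helps as a benchmark, but it comes earlier, at a younger age, and spans the first repeat of the tests; it says nothing directly about M3 to M12.

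Finally, much choice of contrasts may be left to a separate statistical analysis plan. Here, however, sections 3.4 and 4.5 already fix the contrasts.

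**Conclusion.** The point holds as a weakness of a secondary objective and of the reproducibility check. The primary comparison of RAIT with RH at M3 is randomised and is not affected.

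The planned duration estimates carry the whole of any maturation or learning effect. How much that matters depends on a drift and a correlation that the document does not give. Over the ranges assumed, false duration findings run from near zero (Tukey, M6 versus M3) to almost certain (pooled M12 versus M6, ρ = 0.8, drift 0.3), while the randomised M6 contrast stays at about 5%. The reproducibility contrast is too imprecise to support a claim of similarity from non-significance: half-width 0.62 to 0.94 against an expected 1.0 m/s². All these figures assume 16 completers per group and SD 1.1. Section 3.2.3 itself expects dropouts and greater variability in this younger group, so actual precision is likely to be worse.

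**What to change.** In section 4.5:

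- Name the baseline-adjusted PC2 minus PC1 differences at M6 (6 versus 3 months of RAIT) and at M12 (12 versus 9 months) as the controlled evidence for objective 3.
- Label the within-group changes M6 − M3 and M12 − M6 as descriptive and not attributable to RAIT. State that the increment from M6 to M12 cannot be isolated by any contrast, because both groups receive it.
- Report (PC1: M6 − M3) minus (PC2: M3 − M0) with its 95% confidence interval, and make no claim of similarity from a non-significant test.

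This changes wording only; visits, treatment and data stay as they are. It does cost something. The randomised contrasts have low power at this sample size, as shown above, and objective 3 becomes a narrower question: the M12 contrast does not replace a test of the last 6 months. An unbiased but imprecise estimate is still preferable to a tighter one that cannot be attributed to RAIT.
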